#### Secondary outcome measures

Secondary outcome measures include the severity of pain as measured by the NRS (completed with EQ-5D-5L), generic health profile as measured by the SF-12 (completed at baseline and 12 months), use of analgesics (completed with NRS and EQ-5D). In addition, secondary outcome measures include stone clearance measured between 8 and 12 weeks following the initial intervention using renal imaging (CTKUB preferred, but plain x-ray and ultrasound are also acceptable), the maximum dimension of the largest fragment of the treated stone in millimetres, the need for additional treatment (carried out or planned) at 12 weeks post-initial treatment and 12 months post-randomisation, complications during the initial intervention, and intervention-related complications at 12 weeks (categorised by Clavien–Dindo classification) following treatment and up to 12 months post-randomisation. All these will be measured by site staff and entered on the CRF.

We will also record NHS primary and secondary care resources used and their costs, patient costs (out of pocket expenses), and time off work up to 12 months post-randomisation. Data gathered from completion of CRFs by site staff and participant questionnaire at 12 weeks following initial treatment and 12 months post-randomisation will also be recorded.

### Data collection and processing

#### Measuring outcomes

Outcome data will be collected throughout the trial for each participant from consent until 12 months following randomisation. See Table 1 for the schedule of events.

**Table 1 Tab1:** Source and timing of measures

		Timing					
		Intervention (PCNL or first session ESWL/FURS)					
		Weeks post intervention				Additional intervention (pre and post if >12 weeks) or treatment-related hospitalisation	Post- randomisation 12 months
Outcome measure	Source	Baseline^a^	Pre	1 to 11	12		
Health status EQ-5D-5L	PQ	✓	✓	✓	✓	✓	✓
Pain	PQ	✓	✓	✓	✓	✓	✓
Health profile SF12	PQ	✓	✓		✓		✓
Use of analgesics	PQ	✓	✓	✓	✓	✓	✓
Stone clearance (imaging)	CRF				✓^b^		✓
Additional interventions received	CRF&PQ				✓	✓	✓
Complications	CRF&PQ				✓	✓	✓
NHS primary and secondary healthcare use	CRF, PQ		✓		✓	✓	✓
Participant costs	PQ		✓		✓		✓

*CRF* case report form, *PQ* participant completed questionnaire

^a^Baseline is after informed consent has been given but prior to randomisation

^b^stone imaging performed at 8-12 weeks post treatment

#### Data processing

Data collected locally will be input at sites by the local research team. Staff in the trial office will work closely with the local research teams to ensure data are as complete and accurate as possible. Participant questionnaires will be sent from and returned to the trial office in Aberdeen with the exception of the 1- and 2-week questionnaires, which may be distributed by the local research teams. Extensive range and consistency checks will further enhance the quality of the data.

#### Confidentiality

Data are stored in accordance with Good Clinical Practice and with the UK Data Protection Acts 1998 and 2018.

### Sample size, proposed recruitment rate and milestones

#### Sample size

The primary outcome is the AUC measured from multiple completions of the EQ-5D-5L by each participant up to 3 months following initial intervention (FURS, PCNL or first session of ESWL). In order to detect a standard deviation difference of 0.3, with 90% power, and alpha set at 5%, 235 participants per group (470 in total) are required. Such a difference in generic health status is considered clinically relevant and, in terms of treatment effect size, in the small to medium range as observed in other clinical studies. To allow for the anticipated 10% of participants for whom outcome data will be completely missing, and therefore the AUC cannot be calculated, it is proposed to randomise 522 participants in both RCT1 and RCT2, giving a total trial population of 1044 participants.

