#### Recruitment rates

We plan to recruit the trial population from approximately 50 NHS centres across the UK, each recruiting an average of one participant per month to either RCT1 or RCT2. Our plan is to achieve the target of 1044 participants (522 to each RCT) over a 52-month recruitment window.

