## Discussion

The PUrE trial is a large, multi-centre, pragmatic RCT to determine the clinical and cost effectiveness of surgical interventions for stones in the lower pole of the kidney. The primary outcome for the study is participant-reported health status (AUC up to 12 weeks post-intervention calculated from multiple measurements of the EQ-5D-5L).

It is not possible to blind the participants or clinicians in PUrE due to the differing nature of the interventions (invasive versus non-invasive) and their requirements (e.g. anaesthesia, multiple treatments). This may be a source of bias in the trial; however, this is limited by the pragmatic nature of the study, randomisation and concealment of allocation.

The main practical challenge of the study has been participant recruitment. Stone disease has a high recurrence rate [1], and many of those approached will have had a lived experience of treatment and this may influence their willingness to be randomised. Screening data indicates that, of those approached, 30% of patients in RCT1 have a preference for treatment that prevented them from entering the trial, and this figure is higher in RCT2 (41%). A qualitative study was instigated to investigate this further to try and identify some best practises from key sites to disseminate to all researchers. However, we have experienced some difficulties implementing the study, largely due to staff feeling uncomfortable about recruitment consultations being audio-recorded.

Due to the unexpected issues with recruitment, trial timelines have been extended by 18 months to allow us to reach the target for RCT1. Early on in the study it became apparent that RCT2 would not recruit to target as the patient population is not as large for RCT2 (stones >10 and ≤25 mm) as it is for RCT1. This is reflected in the screening data; there have been considerably fewer patients screened for RCT2 compared to RCT1 (252 versus 1036 at the time of writing).

Other than the difficulties previously discussed there have been no major issues conducting the PUrE study.

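### The sample size text still promises 522 participants and 90% power for RCT2, although the same article says RCT2 will miss its target

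*Protocol article*

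**What the plan says.** The Sample size section sets a target difference of 0.3 SD with 90% power and "alpha set at 5%, 235 participants per group (470 in total) are required". It then allows for 10% of participants with no usable outcome: "it is proposed to randomise 522 participants in both RCT1 and RCT2, giving a total trial population of 1044 participants". The Recruitment rates section repeats the target in the present tense: "522 to each RCT) over a 52-month recruitment window".

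The Discussion says something different about RCT2: "Early on in the study it became apparent that RCT2 would not recruit to target". The reason given is a smaller pool of patients with stones above 10 mm. The screening counts for RCT2 and RCT1 are "252 versus 1036 at the time of writing". Treatment preference kept 41% of those approached out of RCT2, against 30% in RCT1. The 18-month extension is explained by the RCT1 target.

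Trial objectives gives RCT2 its own null hypothesis, and Trial design calls both trials superiority trials. Statistical analysis says that the two will be analysed entirely separately.

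**The concern.** One document gives two incompatible accounts of RCT2. The Methods present 522 participants and 90% power as the plan, while the Discussion says that this number will not be reached. The Methods text does not read as an untouched historical statement either. Trial status gives a first recruit in May 2016 and a planned close on 30 September 2020, about 52 to 53 months, which matches the 52-month window in Recruitment rates. The timeline therefore appears to have been brought up to date while the RCT2 target was left standing.

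Because the trials are analysed separately, RCT1 cannot make up for lost information in RCT2. If RCT2 ends well short and its result is non-significant, a reader who relies on the stated 90% could take the result as good evidence that FURS and PCNL do not differ by 0.3 SD. A smaller trial would not support that.

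**Working it through.** **Inputs.** From Sample size: difference 0.3 SD, power 90%, alpha 5%, equal groups, 10% missing, 522 randomised per trial. Sidedness is not stated; two-sided reproduces the figure, whereas one-sided would need only about 191 per group. From Discussion: 252 screened for RCT2, 1036 for RCT1, and 41% of those approached for RCT2 lost to preference.

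**The plan's own figure.** Per group, n = 2(1.96 + 1.2816)² / 0.3² = 2 × 10.507 / 0.09 = 233.5, so 234 by the normal approximation. The two-sample t-test gives 234.5, so 235. Two groups make 470, and 470 / 0.90 = 522.2. The plan's 235, 470 and 522 all reproduce, and power at 235 per group is 90%.

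**RCT2 at smaller sizes.** The article gives no achieved or projected RCT2 number, so each N below is an assumption. With N randomised and 10% missing, each group has n = 0.9N / 2. Power is approximately Φ(0.3 × √(n/2) − 1.96). For N = 261: n = 117.45, √(58.7) = 7.66, 0.3 × 7.66 − 1.96 = 0.34, and Φ(0.34) = 0.63. The table gives t-test results.

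| Assumed N randomised | Basis | n per group | Power at 0.3 SD |
|---|---|---|---|
| 522 | stated target | 234.9 | 90% |
| 390 | needed for 80% power | 175.5 | 80% |
| 261 | half the target | 117.5 | 63% |
| 252 | every patient screened at the time of writing | 113.4 | 61% |
| 149 | 252 × (1 − 0.41) | 67.1 | 41% |
| 127 | 522 × 252/1036 | 57.2 | 36% |

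**Precision at 127.** The 95% confidence interval half-width is about 1.96 × √(2/57.15) = 0.37 SD. The difference detectable with 90% power is 0.61 SD, about twice the planned 0.3 SD.

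**How large the shortfall must be to matter.** A small one would do little harm: 450 randomised still gives about 85%. But the count at the time of writing is 252 screened, not randomised, which is under half of 522 and below the roughly 390 needed for 80%.

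**The case against.** The best defence is that a design calculation is not falsified by slow accrual. The arithmetic is right, the text says what was proposed, and the Discussion openly discloses the shortfall, its cause and the screening counts. Statistical analysis already commits to reporting estimates with 95% confidence intervals, and nothing in the article says that a non-significant result will be read as no difference. Much of this stands. It narrows the point to figures that were not restated, but it does not remove it: the disclosure gives no expected size, power or precision for RCT2, and the two Methods sections carry no qualification.

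Four stronger readings are tempting but not supported:

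- *RCT2 has about one-third power.* The 127 behind 36% assumes that RCT1 reaches exactly 522, that the screening ratio stays constant, and that eligibility and approach rates are equal in the two trials. The 149 applies a percentage of those approached to a count of those screened. Neither is a projection made by the article.
- *A non-significant result is the likely outcome even if the difference is real.* This fails at half the target, where power is 63%.
- *Recruitment to RCT2 has been given up.* The article ties the extension to the RCT1 target; it does not say that RCT2 stops recruiting.
- *The centre rate is also wrong.* A reader might multiply 50 centres by 52 months at "each recruiting an average of one participant per month to either RCT1 or RCT2" and get 2600 instead of 1044. That assumes every centre is open for the whole window, which the article does not say. At one per month, 1044 / 52 is about 20 centres open on average, so no error is shown.

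**Conclusion.** The point holds as an internal contradiction: 522 randomised, 90% power and the 1044 total are still stated for a trial that the same article expects to fall short. The sample size calculation itself is sound, and RCT1 is not affected.

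The existence of the shortfall is certain, because the article states it. Its size is not. Over the scenarios shown, power at 0.3 SD runs from about 63% (261 randomised) down to about 36% (127 randomised), assuming a two-sided 5% test, equal groups and 10% missing outcomes. Recruitment was still open when the counts were given, so the final number could differ. Still, even randomising every patient screened by then would give only about 61%. The correction matters because RCT2 is a separately analysed superiority comparison, and its stated power shapes how a null result will be read.

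**What to change.** 1. In Sample size and Recruitment rates, limit 522 and 90% power to RCT1.
2. For RCT2, state the number now expected, with its power at 0.3 SD, the difference detectable with 90% power and the expected 95% confidence interval width. The sponsor holds the actual recruitment figures and should use those instead of the scaled numbers above.
3. Replace the 1044 total with the RCT1 target plus the expected RCT2 number.
4. State that RCT2 will be interpreted from its estimate and 95% confidence interval set against 0.3 SD, and that p > 0.05 will not be read as no difference. This fits the existing commitment to estimates and intervals.

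No change to the stated centre rate is needed on this ground. The cost is a few sentences in the protocol, carried into the analysis plan, and a less favourable stated power for RCT2. No extra patients are required, and no randomisation or analysis step changes.

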#### Recruitment rates

We plan to recruit the trial population from approximately 50 NHS centres across the UK, each recruiting an average of one participant per month to either RCT1 or RCT2. Our plan is to achieve the target of 1044 participants (522 to each RCT) over a 52-month recruitment window.

### Statistical analysis

The primary outcome — health status AUC — will be generated for each participant using the trapezoidal rule. Data for participants who have missed a scheduled time point will be estimated using a multiple imputation approach to make use of partial outcome data. Sensitivity analyses will be conducted to assess the robustness of the treatment effect estimate to these approaches. The primary outcome measure will be analysed using linear regression with adjustment for design variables. Secondary outcomes will be analysed using generalised linear models with adjustment for design and baseline variables as appropriate. Subgroup analyses will explore the possible modification of treatment effect by important factors (centre, participant body mass index, stone size (maximum dimension and volume), stone density on CTKUB (Hounsfield units), skin to stone distance). We will also explore within each allocated group whether technical factors modify the treatment effect (access sheath versus no access sheath and digital versus non-digital instrument (FURS); fixed-site versus mobile device (ESWL); calibre of access track (PCNL)). This will be done by including treatment-by-factor interactions in the model and they will be classified as exploratory analyses. All analyses will initially be performed on an intention-to-treat basis, although we will consider additional analysis groups such as per-protocol if indicated. The main statistical analyses will be based on all participants as randomised, irrespective of subsequent compliance with the treatment allocation. All treatment effects sizes will be summarised by estimates and 95% CIs from the appropriate models. From the feasibility phase we will report estimates of recruitment rates and potential participant availability, together with appropriate CIs. There are no planned interim outcome analyses; all analyses will occur following completion of trial follow-up. Interim analyses will be performed if requested by the Data Monitoring Committee (DMC).

All analyses will follow a carefully documented statistical analysis plan. RCT1 and RCT2 will be analysed entirely separately. The Trial Steering Committee (TSC) and the independent DMC will be asked to review and comment on the statistical analysis plan prior to analysis. We propose that progress and monitoring of the two RCTs will be undertaken within the same DMC and TSC. The team propose that each study will be analysed once completed. The DMC and TSC will meet before recruitment begins to agree its terms of reference and other procedures.

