#### Follow-up procedures

Eligible patients who have given signed informed consent to participate in the study will be asked to complete the EQ-5D-5L, 12-item short-form survey (SF-12), pain score (by the Numeric Rating Scale (NRS)) and use of analgesic questions at baseline prior to randomisation. A baseline clinical case report form (CRF) will also be completed that will include stone size measured as the maximum dimension on a CTKUB. They will then be randomised to either one of the interventions dependent on the size of the lower pole stone and placed upon the appropriate waiting list. Waiting time duration for the trial interventions will be recorded and monitored. Participants will be asked to complete the pain score (NRS), EQ-5D-5L and use of analgesic questions at a number of fixed and variable time points during their trial participation. Fixed points will be baseline, just prior to initial intervention, weekly up to 12 weeks after initial intervention (FURS, PCNL and first ESWL session) and at 12 months post-randomisation. Variable points after 12 weeks will be just prior and 1 week after any additional intervention (including planned additional sessions of ESWL and removal of stent) and during any other hospital admissions related to treatment of their lower pole kidney stone (such as admissions for pain control or infection). At 12 weeks following the initial intervention, and at 12 months post-randomisation, participants will be asked to complete questions relating to their primary and secondary care use and their associated travel. At 12 months post-randomisation participants will be asked to additionally complete the SF-12. Participants will also be given the opportunity to complete an EQ-5D-5L at their discretion throughout the duration of the trial. A subset of 100 participants will receive the Cambridge Renal Stone Patient Reported Outcome Measure [34], a disease-specific health-related quality of life tool, at baseline, pre-intervention and at 12 weeks post-intervention.

Reminders may be used; for the earlier time points this may be a text message or email on the day that the questionnaire is due and, for the later time points (e.g. 12 weeks and 12 months), this reminder will be sent approximately 2 weeks and 4 weeks after the questionnaire is due.

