### Outcome measures

#### Primary outcome measure

The primary outcome measures are health status measured by EQ-5D-5L AUC to 12 weeks post-intervention, based upon EQ-5D-5L completion at fixed time points (at baseline (recruitment), just prior to initial intervention (FURS, PCNL or first session of ESWL), weekly up to 12 weeks after initial intervention) and at variable time points (just prior to any additional intervention (including planned additional ESWL sessions and removal of stent) and once during hospitalisation for adverse events related to treatment (e.g. pain and infection)), and incremental cost per QALY gained at 12 months post-randomisation based on the estimated NHS costs and participant responses to the EQ-5D-5L (including an additional time point at 12 months).

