#### Cost effectiveness

Cost effectiveness will be measured in terms of costs of the treatment care pathways and QALYs at 12 months post-randomisation for the within-trial analysis. Mean NHS costs, patient costs and QALYs will be compared between randomised groups at 12 months. Incremental costs and QALYs will be estimated for FURS versus ESWL (for participants with stones ≤10 mm) and for FURS versus PCNL (for participants with stones >10 mm and ≤25 mm stones) using linear regression with adjustment for design variables and baseline values as appropriate. The final decision on what regression model to use is data-dependent. However, as the RCT is planned to involve 50 recruitment sites from the UK the use of multi-level regression models will be considered [43]. Uncertainty surrounding joint estimates of incremental cost and effects will be characterised and presented graphically using cost-effectiveness acceptability curves [44, 45]. Guidelines for economic evaluation advocate for a long enough time horizon to consider all cost and consequences relevant for the analysis [39]. In order to assess longer term cost effectiveness, a simple Markov model will be developed using available data on recurrence rates and extrapolation of costs and effects out to 5 years post-randomisation.

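### The primary AUC regression is specified with design variables but not the pre-randomisation EQ-5D-5L, so available precision is forgone and chance baseline imbalance stays in the estimate

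*Protocol article*

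**What the plan says.** The Statistical analysis section of the protocol article gives the covariates for the clinical primary outcome in one sentence: "The primary outcome measure will be analysed using linear regression with adjustment for design variables". The next sentence treats secondary outcomes differently, with "generalised linear models with adjustment for design and baseline variables as appropriate". The Cost effectiveness section takes a similar line for incremental costs and QALYs, "using linear regression with adjustment for design variables and baseline values as appropriate".

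The covariate is collected. Under Follow-up procedures, consenting participants are asked for the EQ-5D-5L and SF-12, together with "pain score (by the Numeric Rating Scale (NRS)) and use of analgesic questions at baseline prior to randomisation". Table 1 shows EQ-5D-5L at baseline and defines baseline as after consent but before randomisation.

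The Primary outcome measure section also lists the baseline reading among the AUC's inputs: "based upon EQ-5D-5L completion at fixed time points (at baseline (recruitment), just prior to initial intervention".

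The article does not name the design variables. Nothing in it suggests that baseline EQ-5D-5L is one of them, and it uses design variables and baseline variables as separate terms.

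**The concern.** The primary outcome is a summary of repeated EQ-5D-5L scores, and the same instrument is scored before allocation. A pre-randomisation measure of the outcome is normally the first covariate to consider in such a regression. Here baseline adjustment is mentioned for the secondary and economic models but not for the clinical primary model.

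Two things are at stake. First, if baseline EQ-5D-5L predicts the AUC at all, leaving it out gives a wider confidence interval than the same data could give. Second, randomisation balances starting health on average but not in any one sample, so a chance difference between arms passes into the unadjusted estimate in proportion to the correlation.

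Both matter more in a smaller trial. The Discussion section says that RCT2 will not recruit to target, and the Statistical analysis section says that the two RCTs are analysed entirely separately, so RCT2 cannot draw strength from RCT1.

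**Working it through.** **Inputs from the protocol article (Sample size):** difference 0.3 SD, power 90%, alpha 5%, 235 per group (470), inflated to 522 for 10% with wholly missing outcome. Two-sided testing is inferred: the null hypotheses are of no difference, and one-sided 5% would need only 191 per arm.

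**Assumed input:** the correlation r between baseline EQ-5D-5L and the AUC. The document gives none, so a range of 0.3 to 0.7 is shown.

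**Step 1. Reproduce the stated size.** n per arm = 2(z₀.₉₇₅ + z₀.₉₀)² / 0.3² = 2(1.960 + 1.282)² / 0.09 = 233.5, so 234. The t-test version gives 234.5, so 235, as stated. 470 / 0.9 = 522.2, which agrees with 522 to within rounding. No covariate is needed to reach these figures. Normal-approximation power at 235 per arm is 90.2%.

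**Step 2. Add the baseline covariate.** The residual SD becomes √(1 − r²), so the required n is 233.5 × (1 − r²), and power = Φ(0.3 / [√(1 − r²) × √(2/n)] − 1.96). At n = 235, √(2/n) = 0.0923; at n = 100 it is 0.1414.

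| r (assumed) | Residual variance | n per arm for 90% | Power at 235 per arm | Power at 100 per arm |
|---|---|---|---|---|
| none (as planned) | 1.00 | 234 | 90.2% | 56.4% |
| 0.3 | 0.91 | 213 | 92.6% | 60.4% |
| 0.4 | 0.84 | 197 | 94.4% | 63.9% |
| 0.5 | 0.75 | 176 | 96.4% | 68.8% |
| 0.6 | 0.64 | 150 | 98.2% | 75.5% |
| 0.7 | 0.51 | 120 | 99.5% | 84.4% |

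The 100-per-arm column is illustrative. The article gives no number randomised or expected for RCT2.

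**Step 3. Size of the chance imbalance.** In SD units, the baseline difference between arms has standard error √(2/n), and an imbalance of size b moves the unadjusted estimate by r × b. With b at its 95% limit:

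- 235 per arm: b = 1.96 × 0.0923 = 0.18 SD. The shift is 0.05, 0.09 or 0.13 SD for r = 0.3, 0.5 or 0.7, which is 18%, 30% or 42% of the 0.3 SD target.
- 100 per arm (illustrative): b = 1.96 × 0.1414 = 0.28 SD. The shift is 0.08, 0.14 or 0.19 SD.

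These are shifts at the edge of what chance would produce; a typical imbalance is smaller. At one standard error, r = 0.5 and 235 per arm, the shift is 0.5 × 0.0923 = 0.046 SD.

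**The case against.** The strongest reply is that nothing stated is wrong. Under randomisation, a regression on design variables gives an unbiased estimate with valid intervals, and the sample size was calculated without a covariate, so the planned analysis and planned power agree. That stands. A reader might infer that the trial is underpowered or its primary estimate biased; the figures support neither.

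It can also be said that the sentence does not exclude baseline, that this is a condensed article, and that an unseen statistical analysis plan may add the covariate. It may. But the article does not leave the covariates open: it names one set for the primary model and a wider one, in the very next sentence, for the secondary outcomes. A plan that followed the text would omit baseline EQ-5D-5L, and one that added it would depart from the published model.

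Third, the gain depends on an assumed r. Participants join a waiting list after baseline, and the AUC covers recovery from a procedure, so the correlation could be modest. This is fair, and is why the range starts at 0.3, where the gain at full size is only about 2 percentage points.

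Two further inferences should be resisted. One is that the AUC and QALY results will conflict because only one is adjusted. The Cost effectiveness section adjusts for baseline only as appropriate and leaves the choice of regression model dependent on the data, and the two outcomes have different horizons (12 weeks after intervention, 12 months after randomisation). A conflict caused by adjustment is possible but not shown. The other is that baseline data will be complete: participants are asked for the questionnaire, which does not guarantee that all return it.

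**Conclusion.** The point holds as a worthwhile improvement to the primary model, not as an error that invalidates it. The article specifies adjustment for design variables and, unlike for its secondary and economic models, mentions no baseline adjustment for the clinical primary outcome, although the relevant score is requested before randomisation.

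At the planned size the forgone power is about 2 to 9 percentage points for r between 0.3 and 0.7, on top of a 90% that is already met. If RCT2 analysed about 100 per arm, the difference would be about 4 to 28 points. Both ranges rest on the assumed r, and the second also on an illustrative size.

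**What to change.** Specify the primary model as linear regression of the AUC on treatment, the design variables and EQ-5D-5L utility at recruitment, before randomisation. Say explicitly that the reading taken just before the initial intervention is not to be used in its place: it follows randomisation and a waiting period in an open-label trial, so it may itself be affected by allocation. Use the same pre-randomisation covariate in the QALY regression, and include it in the multiple imputation model for missed time points.

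Make the change before any outcome comparison is seen, so that it cannot appear data-driven. The cost is a line in the protocol and the analysis plan, one degree of freedom, and a stated rule for missing baseline scores. No new data are needed. The sample size can stay as it is, with the gain kept as extra precision because r is unknown.

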### Interventions to be evaluated

The experimental intervention FURS will be compared with the standard interventions ESWL and PCNL. All three interventions are currently in general use by urology departments throughout the UK NHS. This trial aims to test the interventions in a standard NHS setting so that the results are generalisable to current routine care in the UK. In line with this aim, all procedures will be delivered in NHS facilities and supervised by NHS staff trained and competent in the procedures. All participants will be under the care of a named consultant urologist who, as in standard NHS practice, will be responsible for planning and carrying out the allocated procedure and arranging follow-up. The surgical interventions FURS and PCNL will be carried out by a trained urologist, or by a trainee urologist under the supervision of a senior urologist. They will be supported by the standard team of ward and theatre staff and radiographers. In some centres, a specialist uro-radiologist will also assist with the procedures, particularly with access to the stone. The ESWL intervention can be delivered using any device approved for this purpose including both fixed-site and mobile lithotriptors. Delivery of the treatment will be according to local practice by staff trained in the procedure, typically a radiographer and nurse, and supervised by a urologist. The techniques and equipment used for FURS, PCNL and ESWL continue to evolve and hence will differ in detail between different surgeons and departments. The trial protocol will not mandate the use of any specific detailed technical method for each intervention, but as part of trial initiation of each site the standard procedure including equipment used for FURS, PCNL and ESWL for that site will be recorded on a trial proforma and updated with changes as necessary. It is anticipated that at 8–12 weeks post-intervention participants will receive imaging to assess stone clearance in accordance with usual standard of care.

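### Each technical factor exists in only one arm of its RCT, so a treatment-by-factor interaction at participant level cannot test effect modification and yields only a non-randomised within-arm contrast

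*Protocol article*

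**What the plan says.** The protocol article, under Statistical analysis, sets out two groups of possible modifiers and one method.

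- **Baseline modifiers.** "Subgroup analyses will explore the possible modification of treatment effect by important factors (centre, participant body mass index, stone size", followed by stone density and the distance from skin to stone. These have a value for every participant in both arms.
- **Technical factors.** "We will also explore within each allocated group whether technical factors modify the treatment effect". Each is tagged to a single procedure: "access sheath versus no access sheath and digital versus non-digital instrument (FURS" and "fixed-site versus mobile device (ESWL); calibre of access track (PCNL".
- **Method.** The next sentence reads: "This will be done by including treatment-by-factor interactions in the model and they will be classified as exploratory analyses". No other method is given for the technical factors.

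The following paragraph adds that "RCT1 and RCT2 will be analysed entirely separately". Under Interventions to be evaluated, technique is left to local practice: "The trial protocol will not mandate the use of any specific detailed technical method for each intervention". The same section says that "the standard procedure including equipment used for FURS, PCNL and ESWL for that site will be recorded on a trial proforma".

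**The concern.** An interaction term asks whether the difference between arms changes with the level of a factor. For that, the factor must have levels in both arms. A participant given ESWL has no access sheath, and a participant given FURS has no lithotriptor type or access-track calibre. The stated aim (modification of the treatment effect), the stated setting (within each allocated group) and the stated model (treatment-by-factor interaction) therefore do not fit together for these factors.

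At stake is the reading of the result. A coefficient labelled as an interaction could be taken to show which technique makes FURS better or worse than ESWL or PCNL. In fact it would compare participants within one arm who received different techniques without random assignment.

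**Working it through.** **1. The plan's own figure.** The interaction analyses have no stated sample size. The main one reproduces. For 0.3 SD, 90% power and two-sided 5%, n per arm = 2 × (1.960 + 1.282)² / 0.3² ≈ 233.5, so 234. The t-test version gives 234.5, so 235 as stated. Power at 235 per arm is 90.2%, and 470 / 0.9 = 522.2 against the stated 522. The check below uses 235 per arm and the 0.3 SD scale.

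**2. Which factors enter which model.**

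| RCT | FURS arm only | Comparator arm only | Total |
|---|---|---|---|
| RCT1 (FURS v ESWL) | sheath; digital instrument | fixed-site or mobile device | 3 |
| RCT2 (FURS v PCNL) | sheath; digital instrument | track calibre | 3 |

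**3. Identifiability.** Let T = 1 for FURS and 0 for the comparator, and let F be the technical factor, coded per participant and set to 0 in the arm where it does not exist. The model is E(Y) = b0 + b1·T + b2·F + b3·T·F.

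- FURS-only factor: F is non-zero only where T = 1, so T·F = F. Two columns are identical.
- Comparator-only factor: F is non-zero only where T = 0, so T·F = 0 for everyone. One column is empty.

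Either way the four columns have rank 3. A numerical check of the FURS-only case with 235 per arm gave rank 3 of 4. A factor with values in both arms gave rank 4 of 4.

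**4. What remains after one column is dropped.** Write m1 and m0 for the mean outcome in FURS with and without the technique, and mc for the comparator mean. The apparent difference in treatment effect is (m1 − mc) − (m0 − mc) = m1 − m0. The comparator arm cancels. In a test data set, the retained coefficient and the plain within-arm difference in means were both −0.1589.

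**5. The literal within-group reading.** If the model is fitted inside one allocated group, T is constant. No treatment effect is left to be modified and no interaction can be formed.

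**6. How far the within-arm contrast can mislead (illustration).** None of these inputs comes from the protocol. Assumed: the technique has no effect; about half of participants receive it; a prognostic variable correlates 0.2 to 0.5 with outcome; worse prognosis raises the odds of the technique by 1.5 to 3 per SD; no covariate adjustment; 2000 runs per setting.

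| Correlation | Odds ratio | Bias (SD) | Rejected at 5% |
|---|---|---|---|
| 0.2 | 1.5 | −0.07 | 8% |
| 0.2 | 3 | −0.17 | 26% |
| 0.3 | 2 | −0.18 | 28% |
| 0.5 | 1.5 | −0.19 | 32% |
| 0.5 | 3 | −0.44 | 93% |

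With the same factor known in both arms and the same confounding in each, the interaction had bias within ±0.006 SD and rejected in 4% to 5% of runs, because the confounding cancels between arms.

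**The case against.** Several points can fairly be made for the plan.

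- **The interaction sentence also covers the baseline modifiers.** It does, and for them it is valid. A reader might infer that the whole interaction plan fails; it does not. But the sentence directly follows the technical factors and is the only method offered for them.
- **The text already says the comparison is within each allocated group.** That is a fair description of what can be estimated. It leaves the effect-modification aim and the interaction model without a role for these factors, so the wording still needs to change.
- **The analyses are labelled exploratory.** This stands, and a reader should not infer that the protocol presents them as randomised findings. It makes no such claim. The label lowers the weight placed on a result but does not make an aliased term estimable.
- **Non-identification depends on the coding.** Correct. The article does not say whether the factors are coded per participant or per site. A site-level factor has a value in both arms and gives full rank. A nested model (FURS with the technique v comparator, FURS without v comparator) can also be fitted, but the difference between its two effects is again m1 − m0.
- **Factor definitions belong in the analysis plan.** Detailed coding does. The point rests on an aim and a method that the article states, not on missing detail.

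**Conclusion.** The point holds in a limited form. For technical factors coded per participant, the stated interaction is aliased with the factor in each of the three such analyses per RCT. The only estimable quantity is a within-arm contrast that was not randomised. Because technique is left to local practice, that contrast is open to confounding by surgeon, centre and case-mix.

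The algebra does not depend on sample size. The conclusion assumes participant-level coding, the natural reading of factors tagged to one procedure and explored within each allocated group. The bias range of 0.07 to 0.44 SD illustrates possible size under assumed, unadjusted confounding and is not a forecast for this trial.

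A reader might also infer that the site proforma already supplies sheath use, instrument type or track size for a site-level analysis. The article says only that standard procedure and equipment are recorded, so this has to be checked item by item.

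The primary outcome analysis, the sample size and the baseline subgroup analyses are unaffected. Severity is minor to moderate.

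**What to change.** 1. Restrict treatment-by-factor interactions to the baseline modifiers.
2. Describe the technical-factor analyses as exploratory, observational associations within the arm that received the procedure, adjusted for baseline prognostic factors and centre, with no claim that they modify the treatment effect. Adjustment reduces confounding but cannot be assumed to remove it.
3. Optionally, where the site proforma does record the item, define the factor as the site's standard practice in force at each participant's randomisation, since the proforma is updated over time. Assign that value to both arms and fit the interaction. State that site practice is itself not randomised, that sites with mixed practice may not be classifiable, and that precision is lower than with a participant-level factor.

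Items 1 and 2 cost only a change of wording. Item 3 needs a check of what the proforma holds and a dated link from site to participant. No new participant data are required.
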